## Abstract

**Background:**

The purpose of this study was to describe the rationale and design of a randomized controlled trial analyzing the effects of mesh type (Ultrapro *versus* Prolene mesh) on postoperative pain and well-being following an endoscopic Totally Extraperitoneal (TEP) repair for inguinal hernias (short: TULP trial).

**Methods and design:**

The TULP trial is a prospective, two arm, double blind, randomized controlled trial to assess chronic postoperative pain and quality of life following implantation of a lightweight (Ultrapro) and heavyweight (Prolene) mesh in endoscopic TEP hernia repair. The setting is a high-volume single center hospital, specializing in TEP hernia repair. All patients are operated on by one of four surgeons. Adult male patients (≥18 years of age) with primary, reducible, unilateral inguinal hernias and no contraindications for TEP repair are eligible for inclusion in the study. The primary outcome is substantial chronic postoperative pain, defined as moderate to severe pain persisting ≥ 3 months postoperatively (Numerical Rating Scale, NRS 4–10). Secondary endpoints are the individual development of pain until three years after the TEP procedure, the quality of life (QoL), recurrence rate, patient satisfaction and complications.

**Discussion:**

Large prospective randomized controlled studies with a long follow-up evaluating the incidence of chronic postoperative pain following implantation of lightweight and heavyweight mesh in endoscopic (TEP) hernia repair are limited. By studying the presence of pain and quality of life, but also complications and recurrences in a large patient population, a complete efficiency and feasibility assessment of both mesh types in TEP hernia repair will be performed.

**Trial registration:**

The TULP study is registered in the Dutch Trial Register (NTR2131)

## Background

Inguinal hernia repair is one of the most common surgical procedures worldwide. In The Netherlands, approximately 30,000 hernia repairs are performed annually. The lifetime risk of undergoing a hernia operation is 27 % for men and 3 % for women [1]. The incidence of hernia recurrence has been the primary endpoint in inguinal hernia studies for many years, but with the introduction of the tension-free mesh repair, recurrence rates have dropped significantly to 2 to 3 % [2]. More recently, attention is being paid to several quality of life (QoL) aspects, with time to full recovery and chronic postoperative pain being addressed in particular [1,3].

Chronic pain after inguinal hernia surgery is a common complication. The incidence of chronic postoperative pain after inguinal hernia repair, as described in the literature, varies significantly (10 to 30 %), which is partially explained by the lack of a clear definition [1-4]. The effect of pain on quality of life is significant, since functional limitations of pain in daily life activities are experienced by 2 % to 20 % of the patients [5].

In experienced hands, endoscopic hernia repair techniques are associated with significantly less postoperative pain and an earlier return to normal activities compared to conventional (Lichtenstein) hernia repair [4,6,7]. Totally Extraperitoneal (TEP) is preferred over Transabdominal Preperitoneal (TAPP) hernia repair, since it is less invasive and associated with fewer visceral injuries [2,8]. In addition, recent studies, (in patients treated with a Lichtenstein or TEP procedure), suggest that lightweight meshes may be associated with less chronic postoperative pain compared to heavyweight meshes [9-12]; the latter create maximum mechanical stability and promote the formation of scar tissue, while the properties of the lightweight mesh aim to improve integration in the abdominal wall and prevent the formation of scar tissue [13,14]. There seems to be no (significant) difference in the risk of a recurrent groin hernia between a lightweight and heavyweight mesh [9,12,15].

In addition, since TEP is associated with less chronic postoperative pain compared to a conventional repair (Lichtenstein), an endoscopic TEP hernia repair with implantation of a lightweight mesh could, therefore, be an appealing technique in the prevention of chronic postoperative pain after groin hernia surgery.

The aim of this manuscript is to describe the rationale and design of a large, prospective, double blind, randomized clinical study comparing the results of chronic postoperative pain and quality of life following endoscopic TEP hernia repair with a heavyweight (Prolene) and a lightweight mesh (Ultrapro).

## Methods and design

### Study design

This is a prospective, double blind, randomized clinical trial involving a high-volume hospital in The Netherlands specialized in the TEP technique for inguinal hernia repair (Diakonessenhuis, Utrecht/Zeist, The Netherlands). All hernia operations are performed by four experienced TEP surgeons. Adult (≥18 years) male patients with primary, unilateral inguinal hernias, eligible for TEP hernia repair, are allocated to either lightweight mesh (Ultrapro, Ethicon, a Johnson & Johnson company, Amersfoort, The Netherlands) or heavyweight mesh (Prolene, Ethicon, a Johnson & Johnson company, Amersfoort, The Netherlands) by randomization. The total follow-up of patients is three years. A flowchart of the study with the estimated recruitment targets is shown in Figure 1. The design, conduct and reporting of this study will adhere to the Consolidated Standards of Reporting Trials (CONSORT) guidelines [16].

**Figure 1 F1:**
[figure not shown]
CONSORT flow-diagram, estimated recruitment targets.

### Patient population

A total number of 950 patients will be included in the trial (see “Sample size considerations”). Patients are recruited during their first visit at the outpatient clinic of the participating hospital. Patients are screened for eligibility according to the criteria listed in Table 1. Male patients ≥18 years of age with primary, reducible, unilateral inguinal hernias and no contraindications for endoscopic TEP repair are eligible for inclusion in the study. Based on a previously conducted cohort study, the estimated mean age of patients is 53 (SD ± 14) years, the proportion of patients with a job is approximately 85 % and over 90 % of the patients have an American Society of Anesthesiologists (ASA) 1 or 2 score.

**Table 1 T1:** Inclusion and exclusion criteria

Inclusion criteria:	Exclusion criteria:
- Male gender	- Female gender
- Age ≥18 years	- Bilateral hernia
- Primary, unilateral, reducible inguinal hernia	- Scrotal hernia - Recurrent hernia
- Eligible for TEP (and general anesthesia)	- Strangulated hernias (necessitating emergency hernia repair)
	- Collagen or connective tissue disorders, such as Marfan’s syndrome
	- Likely problems with maintaining follow-up (for example, patients with no fixed address or insufficient comprehension of Dutch language

### Intake

The study information is sent to patients after an appointment is made for an initial consultation. The appointment with one of four surgeons specialized in TEP hernia repair is scheduled within one week. After screening for eligibility criteria, informed consent is obtained and the patient is included in the study. Preoperative patient data are obtained by the coordinating investigator (Table 2).

**Table 2 T2:** Preoperative data

- Age	- Pain:^*^
- ASA-classification	· NRS score
- Co-morbidity (for example other pain syndromes)	· Brief Pain Inventory (BPI)
- Medication	· Inguinal Pain Questionnaire (IPQ)
- Smoking	· Carolinas Comfort Scale (CCS)
- Body Mass Index (BMI) - Education and occupation	· Pain-related Sexual Function Questionnaire (PSF)
- Health-related Quality of Life:^*^	
· SF-36 Questionnaire	
· EQ-5D Questionnaire	

* see section “Follow-up” of the manuscript (pages 7–8).

### Randomization

Patients are randomly assigned to either Ultrapro or Prolene mesh in the operating room (after patients are under general anesthesia) by computerized block randomization. Follow-up of patients will take place according to the intention-to-treat principle. The patient, coordinating investigator and the surgeon involved in the follow-up of enrolled patients are blinded for the allocated mesh. Obviously, the operating surgeon cannot be blinded to the study because of the characteristic composition of the two meshes. To avoid bias, the mesh type is not mentioned in the operating chart. In addition, the follow-up is not by the operating surgeon, but by one of the other three surgeons specialized in hernia repair.

### Intervention

The perioperative care and surgical technique do not differ between the study groups and are not different from the standard procedure. There are no other interventions than the implantation of a lightweight mesh (Ultrapro) or a heavyweight mesh (Prolene) during the TEP endoscopic procedure. General anesthesia is applied in all patients. The operative details of the TEP technique have been described previously [7,17]. The mesh graft is not fixated; it reduces operative time, saves costs and avoids possible entrapment neuralgia. Hernia types are classified during TEP repair according to the Nyhus classification. Intra-operative complications and operative time are registered in the Electronic Patient Chart (Dutch: EPD).

#### *Prolene*

Prolene® is a non-soluble, so-called heavyweight mesh.[14] It is the mesh commonly used in endoscopic TEP hernia repair in our hospital. The mesh characteristics are:

Structure: Monofilament with small pores

Polymer: Polypropylene

Weight: 80 to 85 g/m^2^

Dimensions: 10 x 15 cm

#### *Ultrapro*

Ultrapro® is a lightweight mesh [14]; the monocryl (polyglecapron) is absorbed within 90 to 120 days due to hydrolysis, leaving a lightweight mesh with a pore size of 3 to 4 mm. The mesh characteristics are: 

Structure: Monofilament with large pores (3 to 4 mm)

Polymer: Polypropylene (PP) and Monocryl (Poliglecapron)

Weight: 28 g/m^2^ (part of the polypropylene that is not absorbed

Dimensions: 10 x 15 cm

### Postoperative management

Patients are discharged on the day of surgery, unless complications occur. The duration of hospital stay and postoperative complications are registered in the EPD. At discharge, patients are advised to take analgesics (Paracetamol and, if necessary, Diclofenac), when necessary and avoid strenuous physical activity (lifting, sports) during the first post-operative week. There are no other (physical) restrictions. The type and amount of analgesics used during the first postoperative week are kept in a pain diary.

### Follow-up

Several questionnaires are used for the assessment of pain and quality of life (also to evaluate which questionnaire can best be used to evaluate pain and its effect on quality of life in this patient population).

1) To assess the presence of postoperative pain, the following validated questionnaires are used:

Inguinal Pain Questionnaire (IPQ, Dutch version) [18]

Brief Pain Inventory, Short Form (BP-SF, Dutch version) [19,20]

Carolinas Comfort Scale (CCS, Dutch version) [21]

Numerical Rating Scale (NRS, 0 = no pain, 10 = extremely painful, Dutch version)

2) To measure the health related Quality of Life (QoL) the following validated questionnaires are used:

Short Form (36) Health Survey (SF-36, Dutch version) [22]

EuroQol 5D (EQ-5D, Dutch version) [23]

3) Finally, to assess the presence of pain related to sexual function, the PSF (pain related to sexual function) questionnaire is used, which is a Dutch translation of the questionnaire similar to the one previously described by Aasvang *et al.*[24] and based on the International Index of Erectile Function (IIEF) [25] to assess the presence, frequency, intensity and location of pain during sexual activity and the effect of pain on sexual function.

The patient is requested to record – on a daily basis during the first week immediately following surgery – the pain experienced, as well as the type and amount of analgesics used.

The NRS is used to assess the amount of experienced pain, where 0 = no pain and 10 = extremely painful. BPI and SF-36 questionnaires are filled in at Day 1 and Day 7 following surgery, to determine the effect of pain on daily activities.

After 6 weeks and 3, 12, 24 and 36 months, the IPQ, BPI, CCS, NRS, PSF, SF-36 and EQ-5D questionnaires are completed by the patients. To prevent bias, the questionnaires will be completed at home, or at the visit to the outpatient clinic at three months and one year postoperatively, in the absence of the surgeon or coordinating investigator, before the clinical assessment at the outpatient clinic. Patient satisfaction with the operative procedure is assessed at one week and three months after surgery on a 0 (= very unsatisfactory) to 10 (= very satisfactory) Likert scale.

All patients are examined in the outpatient department by one of the four surgeons (different from the operating surgeon) and the coordinating investigator at three months and one year after surgery. The physical examination is, if necessary, supplemented with an Ultrasound or MRI scan in patients with groin pain and/or complaints suggestive of a recurrent hernia.

All visits include standardized clinical evaluation (according to the validated ‘Inguinal Pain Form (Dutch ‘Liespijnformulier’) by Loos [26]) and registration of possible complications. Parameters assessed at the outpatient evaluation are:

Complications after surgery

Short term (for example: seroma, hematoma, wound-infection, urinary retention, constipation)

Long term (for example: testicular atrophy, mesh infection)

The presence of a recurrent hernia

The presence of a contra-lateral hernia

Other non-hernia related problems in the groin region (for example, hydrocele, varicocele, prostate problems/hidradenitis)

Postoperative pain

Characteristics of pain

The relation of pain to daily activities, physical activity and/or sexual activity

Possible treatment of pain

Mesh feeling

Sensibility disorders in the inguinal/scrotal/thigh/umbilical region or elsewhere

### End-points

The primary endpoint is the presence of moderate to severe chronic pain three months after an endoscopic preperitoneal (TEP) hernia correction, as measured by the NRS. The definition of the International Association for the Study of PAIN (IASP) is used with chronic postoperative pain being defined as pain still present at the site of the operation three months after the primary surgery and different from the pain before the operation. Pain is measured on a 0 (= no pain) to 10 (extremely painful) scale. In accordance with the literature, the following cut-off values for pain are used: [26]

Mild pain: NRS 1 to 3

Moderate pain: NRS 4 to 6

Severe pain: NRS 7 to 10

Moderate to severe pain is considered as clinically relevant [26]. Only moderate to severe pain (NRS 4 to 10) will, therefore, represent ‘chronic pain’ in this study. Secondary endpoints are:

Duration of hospital stay

Complications: intra-operative, post-operative period (until three months after surgery), long-term (until three years after surgery, for example, testicular atrophy)

Time to resume daily activities and return to work

Recurrent hernia

Contra-lateral hernia

Development of pain over time as measured by the NRS score at the first week following TEP repair and 6 weeks, 12, 24 and 36 months postoperatively

Development of pain over time as measured by the BPI, IPQ and CCS questionnaires: the presence of pain in the first week postoperatively and after 6 weeks, 3 months, 12, 24 and 36 months

Development of pain, sensitivity disorders (anesthesia, hypoesthesia, hyperesthesia, allodynia) and or discomfort (including sensation of ‘mesh presence’ at the outpatient visit at three months and one year post-operatively

Health related quality of life as measured by the SF-36 and EQ-5D questionnaires

Pain related sexual function as measured by the PSF questionnaire

Patient satisfaction with the procedure and perioperative care

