### Sample size and power

The most common definition of chronic postoperative pain is from the International Association for the study of pain (IASP), where chronic pain is defined as pain lasting longer than three months following the primary operation, and other than the pain that was experienced preoperatively. The hypothesis is that the incidence of chronic pain is lower after implantation of a lightweight mesh (Ultrapro) than after implantation of a heavyweight mesh (Prolene). Based on a pilot study in our hosopital the assumption is made that 23% of the patients with a Prolene mesh will experience pain three months after TEP repair. In the Ultrapro group a reduction of 7.5% in the incidence of pain is expected. With a two-sided alpha of 0.05 and a power of 0.80, a total of 429 patients are to be included in each allocation group. Based on previous experience, a loss to follow-up of 10% is expected. Therefore, a total of 950 patients will be included in the TULP trial.

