### Statistical methods

Data will be analyzed according to the intention-to-treat principle. SPSS software (SPSS, Chicago, IL, USA) will be used for statistical analysis. Descriptive statistics are used for baseline data. The incidence of the primary endpoint (moderate to severe chronic pain three months after endoscopic TEP repair as based on a NRS 4 to 10) will be compared between the Ultrapro and Prolene mesh group by means of Chi-square analysis. The comparisons of pain will be adjusted for analgesics used as a secondary supporting analysis. The number-needed-to-treat to prevent one case of chronic pain will be calculated. In an additional multiple logistic regression model, the effect of treatment on the primary endpoint will be assessed in relation to important risk factors for pain (younger age, severe pain in the postoperative period and severe preoperative pain [27]). Secondary endpoints will be analyzed by using a Student’s *t*-test (normally distributed continuous), Mann–Whitney analysis (not normally distributed continuous) or Chi-square analysis (categorical variables). The individual development of pain over time will be analyzed with repeated measurement strategies. Effect estimators are described with 95 % confidence intervals. Significance is set at a level of *p ≤ 0.05*.

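### The primary case definition is inconsistent: the adopted chronic pain definition excludes unchanged preoperative pain, while the NRS 4 to 10 rule does not

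*Protocol article*

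**What the plan says.** The protocol article describes the primary endpoint in four places.

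- **Abstract, Methods and design:** "moderate to severe pain persisting ≥ 3 months postoperatively", with NRS 4 to 10 as the measure.
- **End-points:** presence of moderate to severe chronic pain three months after surgery, by NRS. The section states that the IASP definition is used, namely "pain still present at the site of the operation three months after the primary surgery and different from the pain before the operation". After the severity bands it adds: "Only moderate to severe pain (NRS 4 to 10) will, therefore, represent ‘chronic pain’ in this study".
- **Sample size and power:** chronic pain as "pain lasting longer than three months following the primary operation, and other than the pain that was experienced preoperatively", given as the most common definition and placed just before the trial hypothesis. The pilot rate of 23% on Prolene is described only as pain at three months.
- **Statistical methods:** the Chi-square comparison is of "moderate to severe chronic pain three months after endoscopic TEP repair as based on a NRS 4 to 10".

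Preoperative pain enters the analysis only as one of several risk factors in an additional logistic model. Preoperative NRS, BPI and IPQ are collected (Table 2). NRS, IPQ and BPI are repeated at three months (Follow-up), and pain characteristics are recorded at the three-month visit.

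**The concern.** The IASP sentence makes difference from the preoperative pain a condition for being a case. The NRS rule has no such condition, and the article does not say which item, visit or assessor would decide it. The NRS records how much pain there is, not whether it is new. The article also does not say that the three-month score refers only to the operated groin.

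This is the sole primary endpoint. If two readings of the protocol give two event counts, the choice between them can be made after the results are seen. The plan itself treats preoperative pain as relevant, since it lists severe preoperative pain among the important risk factors for the endpoint. A result obtained with the NRS rule but reported as IASP chronic pain would also describe something that was not measured.

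**Working it through.** **1. The texts side by side.**

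| Section | Intensity | Time | Different from preoperative pain? |
|---|---|---|---|
| Abstract | NRS 4 to 10 | persisting at least 3 months | not mentioned |
| End-points, IASP sentence | none | still present at 3 months | required |
| End-points, NRS rule | NRS 4 to 10 | 3 months | not mentioned |
| Sample size and power | none | longer than 3 months | required |
| Statistical methods | NRS 4 to 10 | 3 months | not mentioned |

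**2. A test patient.** Preoperative groin pain is NRS 5. At three months the pain is of the same kind and still NRS 5. Under the NRS rule he is a case. Under the IASP sentence he is not. If the pain were new, both would count him. The two rules differ exactly for patients with NRS 4 or more whose pain is unchanged in kind.

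**3. The plan's own sample size.** Inputs from Sample size and power: 23% on Prolene, a reduction of 7.5 points to 15.5%, two-sided alpha 0.05, power 0.80.

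n per arm = (1.960 + 0.842)² × [0.23 × 0.77 + 0.155 × 0.845] / 0.075² = 7.849 × 0.308075 / 0.005625 = 429.9

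This matches the stated 429. For dropout, 858 / 0.90 = 953, against 950 stated. With 950 randomised and 10% lost, 950 × 0.90 / 2 = 427.5 per arm remain, and power (pooled variance) is 79.5%. The sample size has no arithmetic error. What is unclear is which definition the 23% belongs to.

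**4. Illustration only.** Let q be the share of Prolene cases with unchanged preoperative-type pain. The documents give no q, so 10%, 20% and 30% are assumptions. I also assume that the 23% is an NRS 4 to 10 rate and that the mesh effect is a risk ratio of 0.155 / 0.23 = 0.674 acting only on the other cases.

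- Prolene events expected at 427.5 evaluable: 427.5 × 0.23 = 98.3. The number whose status depends on the sentence followed is 98.3q: 9.8, 19.7 or 29.5.
- NRS rule: Ultrapro rate = 0.23q + 0.23(1 − q) × 0.674.
- Difference condition applied: rates 0.23(1 − q) and 0.23(1 − q) × 0.674.

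| q | NRS rule: rates | power | Difference condition: rates | power |
|---|---|---|---|---|
| 10% | 23% vs 16.25% | 70.1% | 20.7% vs 13.95% | 74.2% |
| 20% | 23% vs 17.0% | 59.2% | 18.4% vs 12.4% | 68.2% |
| 30% | 23% vs 17.75% | 47.8% | 16.1% vs 10.85% | 61.4% |

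These figures show that the two definitions are not interchangeable. They do not estimate the trial's power.

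**The case against.** The best defence is that the NRS sentence in End-points comes last and settles the matter: instrument, cut-off and time agree between End-points and Statistical methods. Another is that Statistical methods uses the term chronic pain, which could carry the IASP condition with it, NRS 4 to 10 being an added severity threshold. Each reading is tenable, but they classify the same patient differently, which is the problem. Nor is this only detail that an article leaves to the full protocol: a condition for being a case is stated, and the endpoint is then stated without it.

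The plan also has a logistic model with preoperative pain. That model is additional to the primary test. It also includes severe postoperative pain, which arises after the mesh is placed, so it cannot stand in for a baseline-adjusted primary comparison.

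Three stronger readings are tempting, and the documents do not support them.

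- **A reader might infer that the planned test cannot apply the IASP condition.** A Chi-square test accepts any binary classification, and relevant data are collected. The gap lies in the case rule.
- **A reader might see persistence as a second conflict.** Persisting for at least three months, and still being present then, both fit one assessment at three months. The wording about lasting longer than three months appears as background. It needs aligning and no more.
- **A reader might take power of 70%, 59% or 48% as a consequence of the plan.** The article states a net reduction of 7.5 points in the incidence of pain. If that already describes all pain at three months, no further dilution applies and power stays near 80%. The lower figures need assumed shares and a recasting of the net reduction as a relative effect on part of the cases.

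**Conclusion.** The point stands as an inconsistency in who counts as a primary case. It concerns patients with NRS 4 or more at three months whose pain does not differ from their preoperative pain. It should be corrected, because it affects the sole primary endpoint and the correction is cheap.

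Its size is unknown, since the documents give no share of such patients and do not tie the 23% to either definition. Under the assumptions above, each 10% of Prolene cases corresponds to about 10 events in that arm. Randomisation balances preoperative pain between arms in expectation, so the NRS rule applied alone would not bias the comparison. The harm is an open choice of endpoint and a mismatch between what is named and what is measured.

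**What to change.** 1. Use one case definition in the Abstract, End-points, Sample size and power, and Statistical methods: NRS 4 to 10 at the operated groin at three months. Remove the condition on difference from preoperative pain from the primary case definition, and align the wording on persisting and on lasting longer than three months.
2. Make the primary comparison a logistic model for that endpoint with mesh and preoperative NRS as the terms, and keep the Chi-square test as supportive. The adjustment accounts for baseline pain; it does not turn the endpoint into new pain, so the report should not call it that.
3. Prespecify one sensitivity endpoint: NRS 4 to 10 at three months and different from the preoperative pain. Classify it blind to mesh from the IPQ and BPI, which are collected both before surgery and at three months, supported by the pain characteristics from the three-month visit. The visit form is not listed among the preoperative data, so the like-for-like comparison has to rest on the questionnaires. Write down the items and the rule before unblinding.
4. State whether the pilot 23% is a rate of NRS 4 to 10 or of any pain. If it is the latter, restate the sample size assumption for the chosen definition.

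The cost is wording, a little more analysis and one blinded classification. No new visits or data are needed.

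### The recovery-time endpoint is assigned to tests that cannot use a censored time; a time-to-event analysis would be a cheap improvement

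*Protocol article*

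**What the plan says.** The End-points section of the protocol article lists "Time to resume daily activities and return to work" as a secondary endpoint.

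Statistical methods assigns the tests by variable type: "Secondary endpoints will be analyzed by using a Student’s *t*-test (normally distributed continuous), Mann–Whitney analysis (not normally distributed continuous) or Chi-square analysis (categorical variables". One other method is named for a secondary outcome, and it is confined to pain: "The individual development of pain over time will be analyzed with repeated measurement strategies". No time-to-event method appears.

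Three other statements bear on the point. Patient population expects that "the proportion of patients with a job is approximately 85" per cent. Sample size and power states that "a loss to follow-up of 10% is expected". Study design states: "The total follow-up of patients is three years".

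**The concern.** A duration is a continuous variable, so the rule in Statistical methods sends this endpoint to the t-test or Mann–Whitney. Both need a completed time from every patient analysed. Two kinds of patient cannot supply one: those lost before they reported recovery, and those still not back to activities or work when last contacted. For both, all that is known is that the time exceeds some value. The stated tests cannot use that information, so the patient is either left out or given a made-up value.

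Exclusion is not neutral. The longer a recovery takes, the more likely it is to be unfinished at last contact, so exclusion removes some of the slowest recoveries. If the excluded patients are unevenly split between the mesh groups, the comparison is biased; even without that, information is lost. At stake is the reading of one secondary endpoint.

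This is not a detail left to an analysis plan that is not shown. The article states a choice of test, and for this endpoint a better one is available.

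**Working it through.** **1. The plan's own figure, to see whether it is touched.** The inputs in Sample size and power are 23% against 15.5% (a reduction of 7.5 percentage points), two-sided alpha 0.05 and power 0.80. The unpooled formula gives

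n = (1.96 + 0.8416)² × (0.23 × 0.77 + 0.155 × 0.845) / 0.075² = 7.849 × 0.3081 / 0.005625 = 429.9 per arm,

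against 429 stated (433 with pooled variance). For 10% loss, 858 / 0.90 gives 954 and 858 × 1.10 gives 944, against 950 stated. The figures reproduce. They rest on the binary primary endpoint, so nothing below changes them.

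**2. Who contributes to each part of the endpoint.** Resumption of daily activities applies to all 950 patients, or 475 per arm. Return to work applies to 950 × 0.85 = 807.5, about 808 patients or 404 per arm. The other 950 × 0.15 = 142.5 have no job to return to.

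**3. How much censoring to expect.** The documents give no recovery times, so the following are assumptions: lognormal times with a log standard deviation of 0.7, and medians of 6 to 14 days. The share not yet recovered at day d is 1 − Φ(ln(d / median) / 0.7).

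- Median 14 days, day 90: ln(90/14) = 1.861, and 1.861 / 0.7 = 2.66, so about 0.4%.
- Median 14 days, day 42: ln(42/14) = 1.099, and 1.099 / 0.7 = 1.57, so about 6%.
- Median 14 days, day 21: ln(21/14) = 0.405, and 0.405 / 0.7 = 0.58, so about 28%.

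If patients are followed to the scheduled three-month visit, hardly anyone is still unrecovered under these assumptions. If information stops earlier, the share rises quickly.

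**4. What the choice of test does.** The simulation used 475 patients per arm and 200 runs, with 10% of patients lost at times spread evenly over the observation window. Mann–Whitney used completed times only; log-rank used all patients.

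| Assumed medians (days) | Observed to day | Censored | Mann–Whitney power | Log-rank power |
|---|---|---|---|---|
| 7 vs 6 | 90 | 1% | 90% | 86% |
| 7 vs 6 | 42 | 2% | 87% | 86% |
| 14 vs 12 | 42 | 8% | 83% | 89% |
| 14 vs 12 | 21 | 28% | 55% | 85% |

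With equal medians (7 vs 7, day 90) the rejection rates were 3.0% and 2.5%. The simulation error is about 2 to 4 percentage points for power, so the first two rows show no clear difference and the last shows a large one.

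**The case against.** The strongest reply is that censoring will be light. Under Postoperative management, patients go home the same day, and activity is restricted only in the first week. Questionnaires follow at six weeks and three months, with a clinic visit at three months. On that schedule nearly everyone should have a completed time, and Mann–Whitney on near-complete times is acceptable. The log-rank test is far ahead only when observation stops at day 21, before those contacts. This stands, and it limits the gain. It does not remove the point: the documents give no recovery times, and the Discussion names follow-up as a main challenge and expects some patients not to return questionnaires.

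A second reply is that Mann–Whitney can give everyone not recovered by a common cut-off the worst tied rank. That is true, but the article states no such rule, and it does not help with a patient lost before the cut-off.

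A reader might go further in three ways that the documents do not support.

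- *Recurrence and contralateral hernia have the same fault.* The article treats these as present or absent over a common planned follow-up, for which chi-square is valid. In a simulation (1,500 runs, 475 per arm, 10% loss in each arm, true recurrence 2.5% in both), estimates were 2.4% with lost patients counted as recurrence-free, 2.6–2.7% with lost patients excluded unless a recurrence had been seen, and 2.5% by Kaplan–Meier. The false-positive rate was 4.9% for chi-square and log-rank alike. At 2.5% against 5%, power was 49–50% for every method. Chi-square fell behind (7.7–9.2% false positives against 5.3%) with 5% against 30% loss and true recurrence of 5% in both arms; nothing in the documents suggests such an imbalance. With scheduled examinations only at three months and one year, Kaplan–Meier would not date recurrences cleanly either.
- *The 15% without a job are lost data.* They are not; the outcome does not apply to them, and any sound analysis leaves them out.
- *The bias is known to run toward no difference.* That needs more unrecovered patients in one particular arm. The trial's hypothesis makes this plausible, but the documents give no figures for it.

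**Conclusion.** The point holds for one secondary endpoint. The article names a duration as an outcome and assigns it to tests that cannot use the time of a patient lost or unrecovered at last contact. That these patients would be excluded is the natural consequence of the stated tests, not something the article says.

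The size is modest and conditional. Under the assumed recovery times, the choice of test makes no clear difference at 1–2% censoring, costs Mann–Whitney about 6 points of power at 8% (89 − 83), and about 30 points at 28% (85 − 55). Follow-up to three months points to the light end. Any bias depends on an uneven split between arms, which cannot be judged from the document. The change is worth making because it is cheap and a time-to-event analysis remains sound across this range.

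**What to change.** In Statistical methods, take this endpoint out of the general rule for secondary endpoints. Analyse time to resumption of daily activities in all patients, and time to return to work in patients employed at baseline, identified from the occupation already recorded in Table 2. For each, give Kaplan–Meier curves, a log-rank test and a Cox hazard ratio with 95% CI, censoring at last contact.

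The cost is a sentence or two of analysis wording and slight extra analysis work. The dataset must hold the dates of resumption, return to work and last contact. The sample size, the primary analysis and the chi-square comparison of recurrence and contralateral hernia stay as they are.
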